### Safety considerations

2.6

Both AT and MT are behavioral, low-risk interventions. Aerobic exercise has been shown to be safe in older and deconditioned individuals and in patients with coronary heart disease.^[37–40]^ The most common adverse effects of exercise include muscle soreness (usually mild and lasting only a few days). Less likely effects include dizziness, faintness, fatigue, or falls. Although rare, exercise may also result in serious side effects such as shortness of breath, chest pain, or cardiac arrhythmias. Protection against these risks includes careful screening, adequate supervision during exercise, and instructing patients to recognize untoward signs and symptoms during exercise. The AT instructor is trained in cardiopulmonary resuscitation and an automated external defibrillator is available at the YMCA facility in the rare case of a cardiac event.

Prior to each exercise session participants complete the revised Physical Activity Readiness Questionnaire^[43]^ to determine whether they have experienced chest pain, shortness of breath, dizziness, or joint or muscle injury since the last session.^[44]^ They are also instructed to recognize the occurrence of symptoms such as chest pain, shortness of breath, numbness, and dizziness during exercise. Should a patient report any of these adverse symptoms before or during exercise, any activity will be immediately stopped and he or she will be referred to their PCP and asked to refrain from any physical activity until receiving a complete medical evaluation. If symptoms are severe the patient will be escorted to the nearest Emergency Department for immediate treatment.

Rarely, MT may produce psychological distress.^[45]^ The distress is typically mild, of short duration, and rarely occurs in the absence of serious ongoing psychiatric conditions. To minimize the likelihood of distress, participants with severe depressive symptoms or ongoing psychosis are excluded from study participation. The MT instructor actively inquires about psychological side effects that might occur during the session or individual practice. If a participant presents with signs of severe psychological discomfort, s/he will be excused from the MT intervention and be screened for suicide risk by a clinical psychologist.

Several protections have also been instituted to protect the privacy and confidentiality of participants, including numerical coding, deidentification, and locked storage of all data. Audio recordings of MT sessions are reviewed promptly to ensure treatment fidelity and then destroyed. Instructions for maintaining privacy and confidentiality are provided to participants at the start of their first MT session, as well as reminders at all subsequent sessions.

### Study assessments

2.7

Assessments are performed at baseline, intervention completion (3 months), and 6 months since baseline (see Table 1). Visits take between 2 and 3 hours to complete and include the completion of study questionnaires, the 6-minute walk test, direct measurements of hip and waist circumference, height, weight, and accelerometer fitting.

**Table 1 T1:**
[figure not shown]
Overview of study measures and timing of assessment.

#### Screening assessments

2.7.1

The 7-day Physical Activity Recall Questionnaire^[36]^ is used to determine physical activity status for screening purposes. Patients are considered physically inactive if they do not meet current recommendations (<150 minutes of moderate-intensity aerobic activity per week OR < 75 minutes of vigorous aerobic activity per week).^[37–40]^ This measure is also administered at 3 and 6 month assessments as a backup in case of accelerometer failure.

The Mini Mental State Examination^[42]^ is used to screen for severe cognitive impairment, with participants scoring less than 24 excluded from the study.

Blood pressure is measured using a Dinamap XL automated blood pressure monitor according to current recommendations.^[46]^ Participants with blood pressure >200/110 or symptomatic orthostatic blood pressure decrease of >20 mm Hg are excluded from the study and referred to their PCP for follow-up.

Depression is assessed with the 7-item depression subscale of the Hospital Anxiety and Depression Scale.^[41]^ Subscale scores range from 0 to 21, with higher scores indicative of greater depressive symptoms. Participants with depression subscale scores >14 are excluded from the study and referred to their PCP.

#### Primary outcomes

2.7.2

Measures of feasibility include the number of screened, eligible, consented, randomized participants, retention rates, session attendance, and individual mindfulness practice. Attendance at MT and AT sessions is recorded using an attendance log. Individual mindfulness practice is tracked using a daily self-report log.

A satisfaction survey is used to assess acceptability. The intervention will be considered acceptable if ≥80% of participants respond that they are at least somewhat satisfied with the intervention.

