## Abstract

**Introduction::**

Despite increasing evidence that aerobic exercise and cognitive training improve cognitive function among patients with cognitive impairment and dementia, few studies have focused on the effect of a combination of these approaches. This study will explore whether combining aerobic training (AT) with mindfulness training (MT), an intervention promoting the moment-to-moment awareness of physical sensations, affective states, and thoughts, improves cognitive function in individuals at risk of dementia. The primary objective is to determine the feasibility and acceptability of the intervention(s). The secondary objective is to obtain estimates of effect sizes on cognitive function and on possible mediators.

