### Population

2.2

This study will enroll 40 patients (10 per condition). Inclusion criteria are: At least 2 risk factors for dementia; Age ≥55; Being physically inactive (defined as not meeting current AHA recommendations for physical activity, that is, <150 minutes of moderate-intensity aerobic activity per week OR < 75 minutes of vigorous aerobic activity per week using the 7-day Physical Activity Recall Questionnaire)^[36–40]^; English fluency; and Ability to understand the study procedures and willingness to commit to the demands of the study protocol. Exclusion criteria include: Inability or unwillingness to provide informed consent; Contraindications to physical activity; Blood pressure >200/110 measured at screening visit; Severe depressive symptoms (Hospital Anxiety and Depression Scale depression subscale score >14)^[41]^; History of psychosis; Severe cognitive impairments (Mini-Mental State Examination score < 24)^[42]^; Hospitalization in the previous 6 weeks; and Current (at least once a month) practice of mindfulness meditation, yoga, or tai chi. In addition, the participant's primary care provider (PCP) written permission to participate in the study is required. This study protocol was approved by The Miriam Hospital Institutional Review Board (IRB).

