### Statistical analyses

2.8

Our choice of sample size (n = 40, 10 participants per condition) was determined by the scope and timeline of this project. Given that this is a proof of concept study, our focus is not on strict hypothesis testing but rather on estimates of effect size and corresponding confidence intervals.

Depending upon variable characteristics (categorical or continuous), Fisher exact test or *t* tests will be used to compare participants at baseline on socio-demographic and medical characteristics. Baseline characteristics not balanced by randomization, as well as variables associated with the study outcomes, will be included as covariates in linear or logistic regression analyses.^[58,59]^

Rates of retention and attendance, as well as program satisfaction scores at 3 and 6 months will be calculated separately for each of the 4 groups. The study will be considered feasible if retention rates of at least 80% are achieved, if participants attend at least 70% of the planned sessions, and if they report completion of at least 70% of the assigned individual home practice exercises. For acceptability, each intervention will be considered acceptable if at least 80% of participants indicate grade 4 enjoyment ratings on a visual scale ranging from 0 to 4.

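### Acceptability, part of the primary objective, has two conflicting success rules: at least somewhat satisfied (section 2.7.2) and the top grade of a 0–4 enjoyment scale (section 2.8)

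*Protocol article*

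**What the plan says.** The Abstract names feasibility and acceptability together as the primary objective.

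Section 2.7.2 (Primary outcomes) gives the measure, "A satisfaction survey is used to assess acceptability", and then the rule: "The intervention will be considered acceptable if ≥80% of participants respond that they are at least somewhat satisfied with the intervention".

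Section 2.8 (Statistical analyses) plans that "program satisfaction scores at 3 and 6 months will be calculated separately for each of the 4 groups". It then sets its own rule, under which an intervention is "considered acceptable if at least 80% of participants indicate grade 4 enjoyment ratings on a visual scale ranging from 0 to 4".

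Section 2.2 (Population) sets 40 participants, 10 per condition. Section 2.8 says that this number "was determined by the scope and timeline of this project". Section 4 (Conclusion) anticipates a fully powered trial if the findings support feasibility and acceptability.

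**The concern.** Both sections reach the same verdict at the same 80% share, but they count different responses. The wording in 2.7.2 implies that more than one answer qualifies. In 2.8 only the maximum grade qualifies. One section speaks of satisfaction and the other of enjoyment. Neither refers to the other, ranks the two, or says where somewhat satisfied falls on the 0–4 scale.

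The article says that its focus is not on strict hypothesis testing, so the feasibility and acceptability benchmarks are the main pass/fail rules it fixes in advance. If one of them has two forms, the report can call an intervention acceptable or not acceptable on the same responses and cite the protocol either way. That verdict informs the step to the larger trial.

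**Working it through.** **No planned figure to reproduce.** The sample size comes from scope and timeline, without a power calculation. The stated total agrees with the arms: 4 × 10 = 40.

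**Inputs from the article**
- Required share: 80% under both rules (2.7.2 and 2.8).
- Arm size: n = 10 (2.2).
- Count needed: 0.8 × 10 = 8 of 10.

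**Inputs assumed (the article gives none)**
- 90% of participants are at least somewhat satisfied.
- 50%, 60%, 70% or 80% give the top grade.
- Everyone responds, and both rules are read from one ordered scale.

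**Step 1: can the rules disagree at all?** Take one arm of 10 in which 5 give grade 4, 4 give a lower grade that still counts as at least somewhat satisfied, and 1 is dissatisfied.
- 2.7.2 rule: (5 + 4)/10 = 90%, pass.
- 2.8 rule: 5/10 = 50%, fail.

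**Step 2: how often?** The probability of meeting a rule is the binomial tail P(X ≥ 8), with X ~ Bin(10, p).
- 2.7.2 rule, p = 0.9: 45(0.9⁸)(0.1²) + 10(0.9⁹)(0.1) + 0.9¹⁰ = 0.194 + 0.387 + 0.349 = 0.930.
- 2.8 rule, p = 0.5: (45 + 10 + 1)/1024 = 0.055.

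On one ordered scale, everyone at the top grade is also at least somewhat satisfied. Meeting the 2.8 rule therefore implies meeting the 2.7.2 rule, and P(pass 2.7.2 and fail 2.8) = P(pass 2.7.2) − P(pass 2.8).

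| Assumed share at top grade | P(pass 2.7.2) | P(pass 2.8) | P(pass 2.7.2, fail 2.8) |
|---|---|---|---|
| 50% | 0.93 | 0.05 | 0.88 |
| 60% | 0.93 | 0.17 | 0.76 |
| 70% | 0.93 | 0.38 | 0.55 |
| 80% | 0.93 | 0.68 | 0.25 |

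**Step 3: other denominators.** For the same four shares, P(pass 2.7.2, fail 2.8) is:
- 0.78, 0.71, 0.56 and 0.31 with 8 respondents per arm (the 80% retention benchmark, 7 of 8 needed);
- 0.95, 0.91, 0.72 and 0.33 with 20 (the two arms that receive a given intervention, 16 of 20 needed).

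Under these assumptions the two rules are certain to agree only if everyone who is at least somewhat satisfied also gives the top grade.

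**The case against.** The strongest reply is that the conflict may be smaller than it looks. The 0–4 visual scale could be an item of the satisfaction survey, since 2.8 speaks of program satisfaction scores just before it gives the enjoyment cut. The content of Table 1, which lists the measures, is not available here. This stands as far as it goes: a reader might infer two separate instruments, but the article does not show that. It does not remove the conflict. On one scale the cut-points differ. On two scales the primary outcome has two unranked definitions.

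A reader might also infer that the 2.7.2 rule accepts any positive answer. The survey's response options are not given, so this cannot be said. Nor does the article state that two separate items are collected, or which rule was intended.

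It can also be said that this is a 40-person proof-of-concept study, that the larger trial is anticipated rather than formally gated, and that neither the effect-size estimates nor safety depend on this rule. All of that is true. It limits the consequences, but acceptability remains a stated success criterion for a primary outcome.

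Finally, a journal article condenses a fuller protocol. That would excuse a missing detail, but here both rules are printed and they disagree.

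**Conclusion.** The contradiction is real. Acceptability has two success rules that share a verdict and a percentage but count different responses, and the article does not say which governs or how the measures relate.

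The contradiction follows from the two sentences alone. Its practical size rests on assumed response rates. With 10 per arm, full response, one ordered scale and 90% at least somewhat satisfied, the chance of passing 2.7.2 while failing 2.8 runs from 0.88 (50% at the top grade) to 0.25 (80% at the top grade). Citing only the upper end would overstate what is known.

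It would go too far to conclude that the 2.8 rule is the mistaken one and that 2.7.2 should stand. A cut at the maximum grade is demanding, but nothing in the article shows that it was unintended.

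**What to change.** Before outcome data are examined, state one acceptability rule in the same words in 2.7.2 and 2.8. It should name:
- one instrument;
- one response cut;
- one time point, since 2.8 plans satisfaction scores at both 3 and 6 months;
- one denominator, either each arm or everyone assigned to a given intervention.

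The sponsor should choose the rule that matches the item actually collected. A cut at somewhat satisfied or better is one option. Any other satisfaction or enjoyment rating should be reported descriptively with its full distribution.

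The authors should also decide how non-responders count, because this changes the rule materially. If 8 of 10 respond and non-responders count as not satisfied, all 8 respondents must be satisfied. At the assumed 90% that has probability 0.9⁸ = 0.43, against 0.93 with full response.

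The cost is a wording change in two sections. If only one item is collected, a stated mapping from its grades to the chosen cut may also be needed.

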#### Secondary outcomes

2.7.3

As a secondary goal we will gather preliminary estimates of the effect of group (MT alone, AT alone, both, or neither) on changes from baseline in cognitive function. We expect that participants assigned to the combined MT + AT condition will achieve larger positive changes in cognitive function compared to either condition alone or none.

Participants are administered a battery of cognitive measures to assess attention (Digital Symbol Substitution Test), executive function (F-A-S verbal fluency test), and episodic memory (International Shopping List Test). Scores from these 3 cognitive domains will be used to calculate a single composite score (Z-scores of Attention, Verbal fluency, and Episodic memory for Non-demented adults [ZAVEN]).^[47]^ Working memory is also assessed using 3 measures available from CogState, Ltd, including the Groton Maze Learning Test, One-Card Learning Task, and One-Back Test.^[48,49]^ Each cognitive measure takes approximately 3 to 5 minutes to complete and is administered electronically using a tablet device. All participants undergo a practice trial prior to the administration of cognitive assessments.

#### Posited mediators

2.7.4

Because there is evidence that RCTs of behavioral interventions based on solid theoretical models are likely to result in larger effect sizes than comparable interventions not based on sound theory, we will explore possible mechanisms by which MT and AT may affect cognitive function. This information will help us to refine the theoretical framework for a future larger RCT.

Accelerometry is used to assess physical activity (Actigraph, LLC, Fort Walton Beach, FL).^[50–52]^ Measures from the accelerometer data include the number of valid days worn, wear time, average step counts per minute, average step counts per day, average minutes of moderate to vigorous physical activity per day, and the average minutes of bouts of this level of activity per day.

The 6-minute walk test is use to assess exercise capacity.^[53]^ This measure is simple, safe, and reliable and performance correlates with peak oxygen uptake.^[54]^

Weight, height, and waist-to-hip ratio are assessed using standardized procedures. A Dinamap XL automated blood pressure monitor is used to measure blood pressure according to current recommendations.

The 12-item Multidimensional Scale of Perceived Social Support^[55,56]^ is used to assess perceptions of support from 3 sources, including family, friends, and a significant other.

Depression is assessed with the 7-item depression subscale of the Hospital Anxiety and Depression Scale (see description in Screening Assessments).^[41]^

Mindfulness is measured using the Five Facets of Mindfulness Questionnaire.^[57]^ This 39-item questionnaire assesses the 5 identified components of mindfulness meditation: observing, describing, acting with awareness, nonjudging of inner experience, and nonreactivity to inner experience.

#### Covariates and moderators

2.7.5

Information about socio-demographic characteristics including age, sex, race/ethnicity, education, income, and insurance status is collected using standard validated self-report forms. A self-report form is used for participants to record current medications and other therapies. Participant medical history pertaining to coronary risk factors, previous myocardial infarction or stroke, comorbidities, and total cholesterol (mg/dL) history is abstracted from electronic medical records.

### Statistical analyses

2.8

Our choice of sample size (n = 40, 10 participants per condition) was determined by the scope and timeline of this project. Given that this is a proof of concept study, our focus is not on strict hypothesis testing but rather on estimates of effect size and corresponding confidence intervals.

Depending upon variable characteristics (categorical or continuous), Fisher exact test or *t* tests will be used to compare participants at baseline on socio-demographic and medical characteristics. Baseline characteristics not balanced by randomization, as well as variables associated with the study outcomes, will be included as covariates in linear or logistic regression analyses.^[58,59]^

Rates of retention and attendance, as well as program satisfaction scores at 3 and 6 months will be calculated separately for each of the 4 groups. The study will be considered feasible if retention rates of at least 80% are achieved, if participants attend at least 70% of the planned sessions, and if they report completion of at least 70% of the assigned individual home practice exercises. For acceptability, each intervention will be considered acceptable if at least 80% of participants indicate grade 4 enjoyment ratings on a visual scale ranging from 0 to 4.

To determine effect sizes on cognitive function, the ZAVEN^[47]^ composite cognitive score will be calculated for each participant by converting Digital Symbol Substitution Test, F-A-S verbal fluency test, and International Shopping List Test scores to standardized z-scores. The effects of group on ZAVEN scores at 3 and 6 month follow-ups will be estimated using a series of mixed effects longitudinal models controlling for baseline. Models will include a subject-specific intercept to adjust for repeated measures of the outcome over time within participant. A single model will allow for all pairwise comparisons between groups (MT + AT vs MT alone, vs AT alone, vs neither) with the goal of estimating effect sizes and corresponding confidence intervals. A similar approach will be used to assess effects of intervention on each measure of working memory (Groton Maze Learning Test; One-Card Learning Task; and One-Back Test). Last, exploratory mediation analyses will be conducted to assess associations between changes in fitness and other mediators at 3 months with changes in cognitive score at 6 months. As sample size is limited for mediation models, our interest in is estimating effect sizes for both the *a* path (group effects on mediators at 3 months) and *b* path (mediators at 3 months on ZAVEN scores at 6 months), using a similar set of mixed effects models as described previously.

To account for missing data, analyses will be performed according to the intention-to-treat approach.^[60]^ If participants withdraw from the intervention they are asked to complete follow-up assessments. If substantial missing data are encountered, possible options include using accepted statistical methods (eg, use of complete data only, use of multiple imputation, and use of modified weights and model-based procedures). Sensitivity analyses will be conducted using different assumptions regarding the mechanism of missingness.

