### Screening and consent procedures

2.4

Initial contact is made via telephone by interested individuals using a dedicated phone number included in all recruitment materials. Patients signaling interest are then invited for a screening visit.

Full informed consent and HIPAA authorization is obtained in person by the senior research assistant (SRA) after a thorough explanation of the study design, study intervention, and the risks and benefits involved. After informed consent procedures are completed, participants undergo a battery of screening assessments (see Study Assessments for details).

Following the screening visit, patients enter a 2-week run-in period during which they wear accelerometers for the assessment of baseline level of physical activity and obtain clearance for participation from their PCP. Accelerometers are fitted during the screening visit and returned via mail using a prestamped envelope.

Information is collected from all individuals assessed for eligibility (ie, individuals who consented but then resulted noneligible at the completion of the screening process) in order to provide a complete CONSORT diagram and description of the recruitment process. This information will also serve as an indicator of future generalizability of the study.

Once all screening assessments are completed participants are randomly assigned (1:1:1:1 ratio) to the 4 different conditions. The randomization schedule was generated in “R” (cran.us.r-project.org) and is based on a permuted block randomization scheme with small, random-sized blocks. The allocation table was uploaded to an ACCESS database to conceal the sequence and the SRA performs randomization by clicking the “randomize” button.

Participants are not blinded to treatment allocation, but are blinded to the study hypothesis. For practical reasons, the MT instructor cannot be blinded, however s/he is not be involved in data management or analysis. Blinded personnel include the Principal Investigator, co-investigators, and all data entry and analysis personnel.

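### Covariates appear to be chosen from baseline tests and outcome associations in the trial's own data, which costs precision in the secondary cognitive estimates at 10 per arm

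*Protocol article*

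**What the plan says.** All places are in the protocol article.

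- **Baseline comparison (2.8 Statistical analyses).** "Fisher exact test or *t* tests will be used to compare participants at baseline on socio-demographic and medical characteristics". No significance level is given, and the text does not say how a two-group test is applied to four arms.
- **Covariate rule (2.8, next sentence).** "Baseline characteristics not balanced by randomization, as well as variables associated with the study outcomes, will be included as covariates". The rule is attached to linear or logistic regression. It has no list of variables, no cap on their number and no definition of balance or association.
- **Candidates (2.7.5 Covariates and moderators).** Socio-demographic: "age, sex, race/ethnicity, education, income, and insurance status". Medical: "coronary risk factors, previous myocardial infarction or stroke, comorbidities, and total cholesterol (mg/dL) history".
- **Cognitive models (2.8, later).** Effects on the ZAVEN composite are estimated by mixed models that control for baseline, and each of three working-memory measures is handled in a similar way. The baseline score is therefore already prespecified.
- **Design.** "Our choice of sample size (n = 40, 10 participants per condition) was determined by the scope and timeline of this project". Under 2.4, "participants are randomly assigned (1:1:1:1 ratio) to the 4 different conditions", using a "permuted block randomization scheme with small, random-sized blocks".
- **Aim.** Section 2.8 puts effect sizes and confidence intervals ahead of strict hypothesis testing.

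**The concern.** The article does not merely leave the covariates to a later document. It states a rule for finding them, and the rule is a poor one for three reasons.

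First, with correct randomisation a baseline difference between arms can only be chance, so testing it answers no question that the trial has. What makes a covariate worth adjusting for is its relation to the outcome, and a test of imbalance does not measure that.

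Second, a t test compares two groups and there are four. One global test, the two factorial margins or all six pairs would select different covariates, and the text does not choose between them.

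Third, if association with the outcomes is judged from the trial's data, the covariate set can differ between ZAVEN and the three working-memory measures. Section 3.1 hopes to see whether benefits are domain-specific or extend across domains. That is harder to judge when each domain is adjusted differently.

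At stake is the precision and comparability of the secondary cognitive effect estimates, which are meant to inform a larger trial.

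**Working it through.** **Inputs from the article.** Four arms of 10, and 4 × 10 = 40, which matches the stated sample size. The article gives no alpha, power, effect size or SD, so there is no power calculation to reproduce.

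**Assumptions.** Two-sided alpha 0.05 for selection, and 12 independent continuous candidates. Section 2.7.5 names 6 socio-demographic items and about 4 to 6 medical ones.

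**1. What the t test can flag at 10 v 10.** Smallest significant observed difference = t(0.975, 18 df) × √(2/10) = 2.101 × 0.447 = 0.94 SD. An observed 0.5 SD difference is never flagged. An observed 1 SD difference is (t = 1/0.447 = 2.24).

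**2. Variables flagged by chance, of 12.**

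| Reading of the t tests | Chance per variable | Expected flags | Chance of at least one |
|---|---|---|---|
| One global test | 0.05 | 12 × 0.05 = 0.6 | 1 − 0.95^12 = 46% |
| Two factorial margins | 1 − 0.95² = 0.0975 | 12 × 0.0975 = 1.2 | 1 − 0.9025^12 = 71% |
| All six pairs (20,000 simulations) | 0.204 | 12 × 0.204 = 2.5 | 1 − 0.796^12 = 94% |

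Categorical candidates tested with Fisher's test give fewer flags. At 10 v 10 with 50% prevalence its actual size is about 1.3% per pair, so six pairs flag at most 6 × 1.3% = 7.8% of the time.

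**3. Screening on the outcome.** At n = 40 the correlation must exceed about 0.31 for p < 0.05. A covariate with true correlation 0.2, 0.3 or 0.4 is picked up in 24%, 48% or 74% of simulated trials.

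**4. Effect on the interval.** The simulation is a single-time-point analysis of covariance for MT + AT v usual care. The baseline score is always in the model (correlation 0.7), there are 12 candidates and no true treatment effect, and 5,000 runs were made per row. A candidate enters if any pairwise t test or its correlation with the outcome gives p < 0.05.

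| Scenario | Baseline only: width | Prespecified set: width | Rule: width | Rule: noise covariates | Rule: each prognostic one selected | Rule: coverage |
|---|---|---|---|---|---|---|
| None prognostic | 1.309 | n/a | 1.412 | 2.95 | n/a | 0.951 |
| Two, coefficient 0.3 | 1.520 | 1.352 | 1.490 | 2.42 | 55% | 0.950 |
| Two, coefficient 0.4 | 1.665 | 1.347 | 1.505 | 2.43 | 69% | 0.950 |

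- Rule v baseline only, none prognostic: 1.412/1.309 = 1.08.
- Rule v prespecified set, two prognostic: 1.490/1.352 = 1.10 and 1.505/1.347 = 1.12.
- Rule v baseline only, two prognostic: 1.490/1.520 = 0.98 and 1.505/1.665 = 0.90.
- Under the margins reading (1,000 runs) the loss is smaller: 1.382/1.309 = 1.06 with none prognostic, and 1.459/1.352 = 1.08 with two at coefficient 0.3.

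**5. Price of the fix if its covariates are useless.** The model with baseline score and arm has 40 − 5 = 35 residual degrees of freedom. Two irrelevant prespecified covariates widen the interval by about √[(35 − 1)/(35 − 2 − 1)] = √(34/32) = 1.03.

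**The case against.** **The reading is inferred.** Section 2.8 does not say that balance is judged by a p-value, and the association clause could mean prognostic variables known from earlier work. That is fair. But the tests stand directly before the rule, no other criterion is offered and no variable is named, so selection from the trial's data is the natural reading.

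**The rule may not govern the cognitive models.** It is tied to linear or logistic regression, whereas the cognitive effects come from mixed models. This stands as an ambiguity, and the fix should settle it.

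**The main predictor is already fixed.** A reader might infer that the plan can miss the most important covariate. It cannot, if the baseline score is the strongest predictor, as is likely. Only the other covariates are at risk.

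**The rule can help.** When prognostic candidates existed, it gave narrower intervals than baseline-only adjustment. That is correct. The comparison it loses is with a prespecified prognostic set.

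**Stronger figures are tempting but unsound.** One could compute 12 × 6 × 0.05 = 3.6 false imbalances, but that counts significant tests. The pairwise tests are correlated, and the number of variables flagged is about 2.5 under the most liberal reading. One could also cite power of 19% or 56% to detect a 0.5 or 1 SD imbalance. Those figures assume a true population difference, which randomisation rules out. For an observed imbalance the 0.94 SD cut-off applies.

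**Bias and the main aim.** A reader might infer biased estimates or damage to the primary objective. Coverage stayed near 95%, so bias is not shown. The runs had no true treatment effect, so they do not settle whether a small shift arises when there is one. Feasibility and acceptability are judged from rates per arm, which the rule does not touch.

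**Conclusion.** The point holds in moderate form. Section 2.8 fixes a poor method for choosing covariates: it tests differences that randomisation makes chance, leaves open how a two-group test serves four arms, and lets the adjusted model depend on the data. Under the all-pairs reading the cost is an interval about 8% wider than baseline-only adjustment if nothing is prognostic, and about 10% to 12% wider than a prespecified prognostic set if two candidates are. It is smaller under the margins reading.

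These sizes rest on the assumed alpha, the number, independence and continuous scale of the candidates, the 0.7 baseline correlation and a single follow-up time. Fisher-tested candidates would lower the false flags. The harm shown is lost precision and an adjustment set that can differ between outcomes. It falls on the secondary cognitive estimates only. In a 40-person study whose stated product is effect sizes with intervals, it is worth correcting.

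**What to change.** In section 2.8:

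1. Delete the baseline significance tests and show baseline data descriptively by arm.
2. Keep the baseline outcome value already specified for the mixed models. Name in advance one short set of prognostic covariates that are already collected, and use the same set for ZAVEN and all three working-memory measures. Age and education are an example; the choice should rest on prior knowledge of what predicts these scores.
3. State that this set replaces the rule that imbalanced or outcome-associated variables "will be included as covariates in linear or logistic regression analyses".
4. Label any further adjustment as a sensitivity analysis.

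The cost is wording only, with no new data and no design change. There are two downsides. A chance imbalance in another variable is handled only in the sensitivity analysis. And if two named covariates prove not to be prognostic, the interval is about 3% wider than with baseline-only adjustment.
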